**Fig. 6 Fig6:**
[figure not shown]
Schedule of enrolment, interventions, and assessments—BathMat trial

### Recruitment strategies

Sites will be selected based on demonstrated capacity to recruit eligible participants, with feasibility assessments undertaken using retrospective audit data to confirm adequate case volume. Each site will maintain a prospective screening log capturing numbers screened, reasons for exclusion, and consent outcomes. These data will be reviewed regularly to monitor progress and identify any emerging barriers to recruitment.

To support consistent enrolment across sites, structured training will be provided to all staff involved in screening and consent. This will cover eligibility criteria, consent procedures, and communication techniques to ensure a clear and consistent approach. Recruitment materials, including posters and participant information leaflets, will be displayed in relevant clinical areas and designed to support understanding of the study and facilitate informed decision-making.

Performance will be reviewed through scheduled recruitment updates and communication between sites. Sites falling below expected recruitment trajectories will receive targeted support, which may include additional training or adjustments to local procedures. The recruitment target has been set based on conservative estimates and accounts for anticipated screen failures and non-consent. A multicentre approach ensures broader access to the eligible population and provides resilience should recruitment at any single site be lower than projected.

### Decision to prone and randomisation

Patients may be recruited to the study once a senior ICU clinician has made the decision to prone them. Any staff member trained to enrol patients may enact enrolment at any time of day or night by ensuring the patient conforms to the inclusion/exclusion criteria, recording patient details in the participant recruitment and randomisation form, and receiving the randomisation details. The recruitment and randomisation form will be accessed via QR code or hyperlink by the trained member of staff, and SealedEnvelope.com will be used for randomisation. Instructions on the form will then direct the randomising staff member to study documents located within their department. If patients are randomised to join the control arm, their first proning session will be carried out in accordance with usual proning and repositioning practices in the recruiting centre. If the patient is randomised to the intervention arm, the BathMat will be placed under the patient during the proning process and will be used for repositioning alongside all other standard care. Randomisation and recruitment to the study can be carried out before or after the patient has been proned in their initial proning session, as long as the patient has not undergone 2 or more repositioning exercises during their initial proning session before recruitment.

Participants will only be identified for recruitment by the direct care team, with any research team then subsequently assisting with the recruitment process as required.

Each proning session is expected to last 16 h in line with Intensive Care Society guidelines, with one proning session per day. There is no maximum or minimum number of repositioning exercises required per proning session, but any period of less than 2 h or more than 4 h between repositioning exercises (i.e. any frequency outside of national guidelines) will be investigated.

### Where patients are proned more than once

If a senior ICU clinician decides that more than one episode of proning is clinically indicated, the method of repositioning will alternate during each subsequent proning session as illustrated below. This illustration is intended for explanation only, and it should be highlighted that the number of times participants in the study are proned will be based solely on clinical indication and decision-making.

If proning is re-employed later in the patient’s ICU stay, the process of alternating the repositioning system will resume. For example, if a patient is proned on day 1 of their ICU admission and is randomised to standard care, and next requires proning on day 5 of the ICU stay, they will be repositioned using the BathMat on day 5, as per the table below.

**Table Tabb:** 

	1 st proning session	2nd proning session (if clinically indicated)	3rd proning session (if clinically indicated)	4th proning session (if clinically indicated)	5th proning session (if clinically indicated)
Randomised to standard care for repositioning	Standard care for repositioning	BathMat for repositioning	Standard care for repositioning	BathMat for repositioning	Standard care for repositioning
Randomised to BathMat for repositioning	BathMat for repositioning	Standard care for repositioning	BathMat for repositioning	Standard care for repositioning	BathMat for repositioning

### Placement of inflatable device

When a proned patient is due to be repositioned using the BathMat, the device will be placed underneath the patient and underneath their sheet either before or after they are proned, but before any repositioning exercise is planned. Participants will be turned prone in accordance with local ICU protocols. The placement of the BathMat will be checked to ensure the shoulder line on the BathMat aligns with the upper edge of the patient’s shoulders, the inflatable device has not wrinkled underneath the patient, and that the device and patient are positioned correctly on the bed. Ultimately, the final position of the patient on the mat must be decided by the clinical team, taking into account the size and shape of the patient but also the size and range of movement of the neck.

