**Methods:**

The BathMat trial is a randomised, multicentre, single-blind crossover study of repositioning in ventilated proned patients in ICU using the BathMat vs conventional care. Ventilated patients who require proning will be randomised to be repositioned with standard care or the BathMat. The same repositioning method will be used throughout each proning session, but will alternate on subsequent proning sessions between BathMat and standard care. The primary outcome is the difference in total staff time (number of staff × total time taken) required to reposition a patient with the BathMat compared with standard care. Secondary outcomes are the number of repositioning exercises performed, the number of adverse incidents associated with repositioning, the ease of manual handling, and the health economic costs of the complications of proning.

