### Removal of device from patient

Once the proning session is completed, the patient will be returned supine as per standard ICU protocol. The inflatable device can be removed immediately before or after returning supine. First, the inflatable device is disconnected from the control unit by squeezing the clasps of the non-interchangeable connector and pulling the two halves apart. The patient can then be rolled to enable the device to be removed.

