### Data entry by clinical team

When enrolled patients require repositioning, the total staff time taken to reposition must be recorded—this is the primary outcome measure. An online clinical data entry Microsoft form, accessible via QR code or hyperlink at the patient’s bedside using any device, will allow staff to submit data from Table 2. Table 3 details domains for repositioning complication. The live Microsoft form will collect patient data linked to the participant’s study number and be managed by the central study team. It will not contain any other identifiable information.

This requires the bedside nurse primarily responsible for patient care to record the time (HH:MM 24-h clock format) at each point of repositioning as stated below, and the number of staff required to do so, by scanning the ‘repositioning QR code for bedside nurse’ unique to that patient or using the appropriate unique uniform resource locator (URL). Time should be rounded to the nearest minute, without the use of decimal places or seconds. The form must be completed after each repositioning manoeuvre and does not require any timing calculations by clinical staff. Instead, the form asks for four data points from the bedside nurse regarding the primary outcome:Repositioning start time: The time when the first staff member required to reposition the patient (in addition to the bedside nurse) enters the bed space to begin repositioning.Repositioning ready time: The time when the last member of staff required to reposition the patient has arrived in the patient’s room or bedspace.Repositioning stop time: The time when the last member of staff who was drawn in to assist the bedside nurse with repositioning has left the patients room or bedspace.The number of staff taken to reposition: Includes all staff (including the bedside nurse) who have helped in the repositioning manoeuvre. This does not include anyone outside of the patient’s room or bedspace who was available for help, and not actively involved in the repositioning manoeuvre.

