It should be noted that statistical analysis will be performed on differences in the time required to gather staff (the difference between repositioning start time and repositioning ready time) and the time required to perform the repositioning exercise (the difference between the repositioning ready time and the repositioning stop time). However, the overall repositioning time (the difference between repositioning start time and repositioning stop time) will be used in the calculation of the primary endpoint.

One member of clinical staff will be expected to complete this data entry exercise every time a patient is repositioned (with or without the BathMat). This is expected to be the bedside nurse looking after the patient, but may be contemporaneously delegated by them to any suitably trained individual.

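### The staff-minutes endpoint leaves out mat placement, connection and removal and charges late-arriving helpers from the start; both enlarge the measured BathMat saving, by an unknown amount that is unlikely to reverse it

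*Protocol article*

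**What the plan says.** The abstract (Methods) defines the endpoint: "The primary outcome is the difference in total staff time (number of staff × total time taken"). Data entry by clinical team fixes the clock for each exercise:

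- Start: "The time when the first staff member required to reposition the patient (in addition to the bedside nurse) enters the bed space to begin repositioning".
- Ready: "The time when the last member of staff required to reposition the patient has arrived in the patient’s room or bedspace".
- Stop: "The time when the last member of staff who was drawn in to assist the bedside nurse with repositioning has left".
- Staff: one number for the exercise, counting the bedside nurse and everyone who helped.

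The same section names the interval that counts ("the difference between repositioning start time and repositioning stop time) will be used in the calculation of the primary endpoint") and also plans separate analyses of start to ready and ready to stop.

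The device steps are described elsewhere. Under Placement of inflatable device, the mat goes beneath the patient "either before or after they are proned, but before any repositioning exercise is planned", and its position is then checked. Under Connection to control unit, the control unit is attached once the mat is in place. Under Removal of device from patient, the mat comes out around the return to supine: "The patient can then be rolled to enable the device to be removed". Table 2, the form completed after each exercise, has no entry for the time or staff these steps take. Table 5 asks how easy the mat was to introduce, not how long it took.

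**The concern.** The stated aim is the change in total staff time when the BathMat is used. Two features of the measure work in the device's favour.

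First, placement, checking, connection and removal are staff work that only BathMat sessions need, and no timed interval covers them.

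Second, a single staff count multiplied by the whole interval treats every helper as present from start, although before ready at least one has not yet arrived. In the expected two-person BathMat turn (bedside nurse plus one helper) the first helper is also the last, so start equals ready and nothing is overcharged. In a turn with five or more staff there is normally a gathering period, and all of it is multiplied by the full count.

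The protocol says the findings will support performance claims for the device and regulatory planning (Statistical analysis). The size of the saving therefore matters as well as its sign. Handling time that is not recorded cannot be recovered later by any analysis plan.

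**Working it through.** **Inputs from the protocol.** Standard care: at least 5 staff, 30–60 min. BathMat: 2 staff, 10 min (Background and rationale; Inflation for repositioning with device). Repositionings per session in the power simulation: 2, 3 or 4 with proportions 1/5, 3/10, 1/2 (Sample size). Target difference: 10 min.

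**Assumptions.** The protocol gives neither a gathering time nor a handling time. I take G (start to ready, standard care) as 5–15 min and W (mat handling per session) as 0–150 staff-minutes.

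**1. Saving implied by the protocol's figures.** 5×30 − 2×10 = 130 and 5×60 − 2×10 = 280 staff-minutes per exercise. If the gap is only the 10 min used for power (20 against 10 min), it is 5×20 − 2×10 = 80.

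**2. Overcharge while gathering, 5 staff.** Charged: 5G. With the nurse present throughout and four helpers arriving at 0, G/3, 2G/3 and G, the absent time is 0 + G/3 + 2G/3 + G = 2G, so 3G is real. If the last three arrive together at G, the excess is 3G. For G = 5 the excess is 10–15 of 25 staff-minutes; for G = 10 it is 20–30 of 50. For two staff G = 0 and the excess is 0.

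**3. Omitted handling.** Mean exercises per session: 2×0.2 + 3×0.3 + 4×0.5 = 3.3. Per exercise, W = 20, 50, 100 gives 20/3.3 = 6.1, 50/3.3 = 15.2, 100/3.3 = 30.3 staff-minutes. With more exercises per session the share falls: a 16 h session repositioned every 2 h has up to 16/2 − 1 = 7, and 50/7 = 7.1.

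**4. Combined.** Corrected saving = measured saving − 2G − W/3.3 (reduction in brackets).

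| G (min) | W per session | 20 vs 10 min | 30 vs 10 min | 60 vs 10 min |
|---|---|---|---|---|
| as measured | – | 80 | 130 | 280 |
| 5 | 0 | 70 (12.5%) | 120 (8%) | 270 (4%) |
| 5 | 20 | 63.9 (20%) | 113.9 (12%) | 263.9 (6%) |
| 5 | 50 | 54.8 (31%) | 104.8 (19%) | 254.8 (9%) |
| 10 | 100 | 29.7 (63%) | 79.7 (39%) | 229.7 (18%) |
| 15 | 150 | 4.5 (94%) | 54.5 (58%) | 204.5 (27%) |

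With the 3G maximum, each corrected figure falls by a further G. Only the extreme last row of the 20-min column then turns negative (80 − 45 − 45.5 = −10.5). On the protocol's own 30–60 min none does.

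**5. What the recorded times can bound.** Lower bound: 2×(ready − start) + staff×(stop − ready). Upper bound: staff×(stop − start), the primary measure. For 5 staff, 30 min and G = 10: lower 2×10 + 5×20 = 120, upper 150, even arrivals 130. For two staff and 10 min both bounds are 20.

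**The case against.** The strongest reply is that this is a choice of scope. Table 1 sets the primary objective per repositioning exercise, whereas placement and removal happen once per session. Decision to prone and randomisation has the mat placed during the proning turn, and removal may coincide with the return to supine, when a team is already at the bedside. Much of this stands: the additional cost may be close to zero in such sessions, and the text allows a roll at removal without saying one is always needed. It does not stand for every session, because the protocol also permits placement, and even randomisation, after the patient is already prone.

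Second, the timing rule is the same in both arms, and having no team to assemble is a real benefit of a two-person method. That is right, and the first helper's waiting is a real cost. The excess is only the charge for helpers not yet there. Against that, time helpers spend travelling or preparing before they enter the bedspace is uncounted except where the charged interval happens to cover it. More helpers incur it in standard care, so 2G is not a clean estimate of bias.

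Third, a reader might infer that the planned significance tests are biased by the overcharge. Statistical analysis does not support that: it models repositioning time and number of staff separately, and the per-helper overcharge enters only their product. Gathering minutes do enter the time model, but as genuine elapsed minutes. The separate start–ready and ready–stop analyses also expose part of the effect.

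Fourth, sensitivity analyses may sit in a full protocol or analysis plan that is not shown. That covers the bounds, but not handling time for which the published data list has no field.

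**Conclusion.** The point holds in a limited form. The product of staff and time omits work that only the BathMat needs and overcharges only turns with more than two staff, so both effects enlarge the measured saving. With G of 5–10 min and 20–100 staff-minutes of handling per session, the 130–280 staff-minutes implied by the protocol shrink by 6–39%. They shrink proportionately more if the true gap is nearer 10 min.

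These sizes rest on assumed gathering and handling times, evenly spaced arrivals, exactly two staff in BathMat turns with the bedside nurse as one of them, and 3.3 exercises per session. A BathMat turn with three or more staff would be charged in the same way as standard care.

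A reader might conclude that the saving is an artefact of the measure. The documents do not support that: on the protocol's own contrast no scenario examined reverses it. Nor do they show that handling time is large; it is simply not recorded.

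**What to change.** 1. For the remaining BathMat sessions, add two entries to the form: number of staff and additional minutes for placement/connection, and the same for removal. Enter zero where the step was absorbed in the proning or supine turn.
2. Report staff-minutes per session with these added, beside the primary result. For sessions already completed, use a stated range.
3. Pre-specify a sensitivity analysis that bounds staff-minutes between 2×(ready − start) + staff×(stop − ready) and staff×(stop − start). The first expression is a lower bound on the gathering charge, not a corrected estimate: with even arrivals it credits 2G where 3G was worked, and so understates standard care by G.
4. Keep the primary endpoint, and do not make a claimed saving depend on both versions. That would add a second success criterion during recruitment.

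Cost: two form entries and one derived variable. Recruitment began in May 2025 and is expected to run to about July 2026, so set-up data will be incomplete for earlier sessions. The saving reported beside the primary result will be somewhat smaller.

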### Connection to control unit

Once the BathMat is appropriately positioned, the control unit is attached via the non-interchangeable connector. The clasps on either side of the connector should be checked to ensure they have adequately sealed the inflatable mat to the control unit.

### Inflation for repositioning with device

When a patient in the intervention (BathMat) group requires repositioning, the member of staff directly caring for the patient will contact relevant team members to assist with repositioning and prepare the patient. For repositioning with the device, a total of two members of staff are expected to be required. If more are used, the reason for this will be documented on the online form by the clinical team.

Once the patient is prepared, one suitably trained member of staff will control the patient’s head and airway, with a second team member using the control device. Inflation of individual vessels is controlled by the buttons on the control device, as seen in Fig. 4. Upwards arrows inflate the vessels, and downwards arrows deflate the vessels. Inflation is complete when the team assess the patient to be adequately lifted to allow repositioning. The maximum pressure that can be achieved in the vessel corresponds to the input pressure, and the vessel will stop inflating if this maximum pressure is achieved. Following rotation of the head, the device is fully deflated. The patient’s arms are moved when the patient has been returned to rest on the bed. Arm positioning is determined by standard unit protocols. The BathMat must always be left fully deflated in between repositioning sessions.

Repositioning in both groups must be performed every 2–4 h as per Intensive Care Society guidelines. At each point that this frequency is not achieved, the reasoning will be documented by the clinical team using the online data entry form, and will be recorded by the research team.

### Removal of device from patient

Once the proning session is completed, the patient will be returned supine as per standard ICU protocol. The inflatable device can be removed immediately before or after returning supine. First, the inflatable device is disconnected from the control unit by squeezing the clasps of the non-interchangeable connector and pulling the two halves apart. The patient can then be rolled to enable the device to be removed.

### Repositioning during standard care

Repositioning for patients during standard care will be performed as per local ICU protocol, every 2–4 h as per Intensive Care Society guidelines. If this frequency is not achieved, the reasoning will be documented in the clinician data entry form.

### Data entry by clinical team

When enrolled patients require repositioning, the total staff time taken to reposition must be recorded—this is the primary outcome measure. An online clinical data entry Microsoft form, accessible via QR code or hyperlink at the patient’s bedside using any device, will allow staff to submit data from Table 2. Table 3 details domains for repositioning complication. The live Microsoft form will collect patient data linked to the participant’s study number and be managed by the central study team. It will not contain any other identifiable information.

This requires the bedside nurse primarily responsible for patient care to record the time (HH:MM 24-h clock format) at each point of repositioning as stated below, and the number of staff required to do so, by scanning the ‘repositioning QR code for bedside nurse’ unique to that patient or using the appropriate unique uniform resource locator (URL). Time should be rounded to the nearest minute, without the use of decimal places or seconds. The form must be completed after each repositioning manoeuvre and does not require any timing calculations by clinical staff. Instead, the form asks for four data points from the bedside nurse regarding the primary outcome:Repositioning start time: The time when the first staff member required to reposition the patient (in addition to the bedside nurse) enters the bed space to begin repositioning.Repositioning ready time: The time when the last member of staff required to reposition the patient has arrived in the patient’s room or bedspace.Repositioning stop time: The time when the last member of staff who was drawn in to assist the bedside nurse with repositioning has left the patients room or bedspace.The number of staff taken to reposition: Includes all staff (including the bedside nurse) who have helped in the repositioning manoeuvre. This does not include anyone outside of the patient’s room or bedspace who was available for help, and not actively involved in the repositioning manoeuvre.

It should be noted that statistical analysis will be performed on differences in the time required to gather staff (the difference between repositioning start time and repositioning ready time) and the time required to perform the repositioning exercise (the difference between the repositioning ready time and the repositioning stop time). However, the overall repositioning time (the difference between repositioning start time and repositioning stop time) will be used in the calculation of the primary endpoint.

One member of clinical staff will be expected to complete this data entry exercise every time a patient is repositioned (with or without the BathMat). This is expected to be the bedside nurse looking after the patient, but may be contemporaneously delegated by them to any suitably trained individual.

